# Clinical study of Tongdu Shujin decoction in the treatment of ankylosing spondylitis with cold-dampness obstruction type: Study protocol for a randomized controlled trial

**DOI:** 10.1097/MD.0000000000032852

**Published:** 2023-02-10

**Keywords:** ankylosing spondylitis, clinical efficacy, pain, stiffness, traditional Chinese medicine

## Abstract

**Methods::**

In this randomized controlled trial, 80 eligible patients were randomly assigned in a 1:1 ratio to a treatment group TDSJ and a control group (celecoxib capsules in combination with thalidomide tablets) for 8 weeks. Visual analogue scale, bath ankylosing spondylitis disease activity index, bath ankylosing spondylitis functional index, and traditional Chinese medicine syndrome scores will be used as primary indicators. Erythrocyte sedimentation rate, C-reactive protein, spinal mobility (figure-ground distance, occipital tubercle-wall distance, Schober test) will be used as secondary indicators. Vital signs (respiration, heart rate, body temperature, blood pressure, electrocardiogram), blood routine, urine routine, stool routine, liver function, and renal function will be used as safety indicators. The primary and secondary indicators will be detected at 0th and 8th week, while safety indicators at 0th, 4th, and 8th week.

**Discussion::**

This study will provide high-quality clinical evidence for the efficacy and safety of TDSJ in the treatment of AS.

## 1. Introduction

Ankylosing spondylitis (AS) is a chronic inflammatory disease mainly of the sacroiliac joint and spinal erosion, patients could have joint pain, stiffness and limited range of motion, and in severe cases, spinal deformity and joint fusion. The incidence of AS in China is about 0.2% to 0.4%, the ratio of men and women is 2 to 3:1,^[1]^ the age of onset is mainly concentrated in 15 to 40 years old, and the peak time is 20 to 30 years old,^[2]^ which is a common disease and frequent incidence in Rheumatology and Immunology Department. AS inflammatory infiltration can lead to sacroiliac joint erosion, spinal adhesion calcification and even fusion, severe cases can involve peripheral joints causing hip fusion and disability, and AS hip joint involvement rate is as high as 60%.^[3]^ The high disability rate has a very negative impact on the physical, psychological and social life towards patients.

It was found that Tongdu Shujin decoction (TDSJ) had a good effect in the treatment of AS with cold-dampness obstruction type by clinical observation. Therefore, we designed this trail to evaluate the clinical efficacy and safety of TDSJ in the treatment of AS with cold-dampness obstruction type, hoping to provide high-quality clinical evidence for the treatment of ankylosing spondylitis with traditional Chinese medicine (TCM).

**Figure 1. F1:**
[figure not shown]
Research flow chart.

### 2.2. Ethic approval

This protocol was carried out in accordance with the principles of the Declaration of Helsinki,^[4]^ and it had been approved by the ethics review committee of the first affiliated hospital of Henan university of Chinese medicine (approval number: 2022HL-424-01) and the whole process was followed up. We registered the study with the Chinese clinical trials registry (registration number ChiCTR2300067535).

### 2.3. Participants

After obtaining informed consent, this study will include 80 AS patients with cold-dampness obstruction type. We will post printed recruitment posters in the hospital or post recruitment information on hospital social media to recruit participants, and participants who meet the research criteria will be invited to the Rheumatology and Immunology Department of the First Affiliated Hospital of Henan University of Chinese Medicine for the research. Eligible participants will be randomized 1:1 to treatment and control groups. The treatment will last 8 weeks.

#### 2.3.1. Diagnostic criteria.

Adoption of the New York Standard revised in 1984^[5]^

Clinical criteria: The course of low back pain lasted at least 3 months, and the pain improved with activity, rest did not decrease; The movement of the lumbar spine is restricted in the anteroposterior and lateral flexion directions; The thoracic extension range is < the normal value of the same age and sex.

Radiological criteria: bilateral sacroiliitis ≥ grade II, or unilateral sacroiliitis grade III to IV.

AS is confirmed if the patient has radiological criteria and any one of the clinical criteria is appended. Diagnosis of probable AS is achieved in those who meet only 3 clinical criteria, or only those who meet radiologic criteria.

#### 2.3.2. Diagnostic criteria for TCM syndrome.

Referring to the dialectical standard of TCM on ankylosing spondylitis in the “Guidelines for Clinical Research of New Chinese Medicines”^[6]^ issued by the National Medical Products Administration, it is proved to be cold-dampness obstruction type.

Primary symptoms: lumbosacral pain, back pain, limited lumbar spinal movement, morning stiffness, fever, redness, swelling and heat pain in the joints of the limbs, swelling and pain in the eyes.

Secondary symptoms: thirst or dry mouth, heavy limbs, dry stools, yellow urine.

Tongue veins: red tongue, moss yellow or yellow thick, smooth pulse.

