#### 2.3.3. Inclusion criteria.

The inclusion criteria are as follows: Meet the Western medical diagnostic standards of AS; TCM dialectic is cold-dampness obstruction type; 18 to 40 years old, male or female; Women of childbearing age ascertain to be non-pregnant and had no pregnancy plans for the duration of the trial; Did not take any AS treatment drugs in the 1 month period before receiving treatment; Voluntarily participate in this trial and agree to enter the clinical study, sign the informed consent form.

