AS with cold-dampness obstruction type is caused by cold and humidity leading to blood coagulation, causing muscle and joint stiffness and pain. TDSJ has the effect of warming, dispelling dampness, channeling and relieving pain. AS is mainly manifested as an inflammatory response accompanied by bone destruction, microglia are activated to produce a variety of pro-inflammatory cytokines combined with neurons, neuronal excitability is enhanced and pain occurs. Modern pharmacology shows that most of the drugs in TDSJ have anti-inflammatory and analgesic effects. Astragaloside IV in astragalus inhibits the secretion of cytokines and the expression of inflammation-related genes,^[11]^ and inhibits the development of inflammation by regulating the MAPK and STAT pathways.^[12,13]^ Coix seed extract reduces pro-inflammatory factor levels and COX-2 expression.^[14]^ Puerarin, the active component of pueraria lobata, can significantly inhibit the expression of mRNA of inflammatory mediators interleukin-1β (IL-1β), interleukin-6 (IL-6), and tumor necrosis factor-α, and significantly improve inflammatory pain.^[15]^ Asperosaponin VI, the component contained in the dipsacus asperoides could significantly inhibit RANKL-induced osteoclast formation and bone resorption activity by suppressing the formation of actin ring. It also inhibited the expression of various osteoblastic marker genes and signaling pathways, and can improve bone destruction caused by inflammation.^[16]^ Taxilli herba extracts significantly reduce levels of pro-inflammatory factors and inhibit inflammatory responses.^[17–19]^ Naringin is the main active substance of rhizoma drynariae, which can boost autophagic flux through SIRT1 upregulation via AMPK activation, thus protecting cells against inflammatory response, oxidative stress, and impaired cellular homeostasis.^[20]^ Eucommia extract can reduce serum IL-6 and IL-17 levels and relieve inflammation.^[21]^ The anti-inflammatory effect of rehmannia glutinosa is also particularly obvious, and its active ingredient catalpol can significantly decreased the expression of NF-*κ*B/NLRP3 inflammatory axis and inflammatory factors, inhibit tissue inflammation and relieve pain.^[22]^ Meanwhile, its active ingredient aucubin also has anti-inflammatory and antioxidant pharmacological effects.^[23]^ Pyrola extract inhibits phosphorylation of p38 MAPK and NF-*κ*B, inhibits the expression of inducible nitric oxide synthase inducible nitric oxide synthase, iNOS and exerts anti-inflammatory effects.^[24]^ Paeoniae alba has obvious analgesic, anti-inflammatory and immune regulating effects, and its active ingredient paeoniflorin can downregulate the NLRP3 inflammasome pathway to reduce inflammation,^[25]^ has a 2-way regulatory effect on the value-added of immune cells, and can reduce the production and release of prostaglandin E2 in the cerebral cortex,^[26]^ and is often used clinically to treat and relieve various types of pain and immune disorders. Achyranthes bidentata saponin has been shown to have osteoprotective effects on the inflammatory response induced by IL-1β stimulation, improving cellular inflammation and apoptosis.^[27]^ Chuanxiong and angelica extracts exert anti-inflammatory effects by hindering inflammatory signaling.^[28,29]^ The active ingredient of Safflower, safflower yellow, has anti-inflammatory, analgesic, and immune regulation functions.^[30]^ Both clematis chinensis and angelicae pubescentis radix extract exert anti-inflammatory effects by reducing pro-inflammatory cytokine levels.^[31,32]^ Corydecumine G (Cor G), the active ingredient of corydilis yanhusuo, has the effect of inhibiting neuronal excitation, thereby relieving pain symptoms.^[33]^ Licorice extract can inhibit the activation of a variety of inflammasome and downregulate NF-*κ*B expression, thereby reducing oxidative stress, inflammation, and pain response.^[34]^

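### The signs printed for diagnosing the cold-dampness type include heat signs and no cold sign, contradicting the inclusion criterion and the protocol's own account of that type

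*Protocol article*

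**What the plan says.** Section 2.3 fixes the population: "this study will include 80 AS patients with cold-dampness obstruction type". Section 2.3.3 makes the type a condition of entry: "TCM dialectic is cold-dampness obstruction type".

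Section 2.3.2 says how the type is recognised. It refers to a national guideline on clinical research of new Chinese medicines, by which "it is proved to be cold-dampness obstruction type", and then prints three lists:

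- Primary symptoms open with lumbosacral and back pain and restricted lumbar movement, continue with "morning stiffness, fever, redness, swelling and heat pain in the joints of the limbs", and end with swollen, painful eyes.
- Secondary symptoms are "thirst or dry mouth, heavy limbs, dry stools, yellow urine".
- Tongue and pulse are "red tongue, moss yellow or yellow thick, smooth pulse".

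The section does not say how many signs, or which combination, are needed.

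Section 5 gives the protocol's own account of the type and of the treatment: "AS with cold-dampness obstruction type is caused by cold and humidity leading to blood coagulation", and "TDSJ has the effect of warming, dispelling dampness, channeling and relieving pain".

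**The concern.** A diagnostic list should describe the condition it is used to identify. Here the label is a cold pattern, the rationale is a warming formula for a cold pattern, and the printed list contains fever and hot, red joints with nothing cold beside them. An investigator who screens from the list and one who screens from the label could admit different patients.

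What is at stake is the population the result describes. The trial asks whether the decoction works in cold-dampness disease. If entry followed the list, some or many participants could have a heat pattern, cold-type patients who lack the listed signs could be turned away, and the report would still carry the cold-dampness name. A reader could not tell from the article which population was studied.

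**Working it through.** There is no figure to reproduce; the check sets the protocol's sections against each other.

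**Step 1: what entry requires.** Sections 2.3 and 2.3.3 require the cold-dampness type. Section 5 says that type arises from cold and humidity.

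**Step 2: classify the items in section 2.3.2.** Taking red, swollen, hot joints as one item, the list has 7 primary symptoms, 4 secondary symptoms and 3 tongue and pulse signs: 7 + 4 + 3 = 14.

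| Group | Items | Count |
|---|---|---|
| Heat, on the wording alone | fever; red, swollen, hot painful limb joints | 2 |
| Heat, if the usual TCM reading is assumed | eye swelling and pain; thirst or dry mouth; dry stools; yellow urine; red tongue; yellow coating | 6 |
| General features of the disease | lumbosacral pain; back pain; limited lumbar movement; morning stiffness | 4 |
| Dampness or not temperature-specific | heavy limbs; smooth pulse | 2 |
| Cold | none | 0 |

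The check is 2 + 6 + 4 + 2 + 0 = 14. The second row is an assumption, because the protocol does not itself label those six items as heat signs. Without it, 2 of 14 items point to heat; with it, 2 + 6 = 8 of 14 do. Either way no item mentions cold, for example pain brought on by cold or eased by warmth, so every item classed as hot or cold points to heat.

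**Step 3: compare.** The name of the type, the inclusion criterion and the account in section 5 all say cold. The items in section 2.3.2 that bear on temperature say heat. No other section reconciles the two.

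**Step 4: follow each text through.**

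- If the list governs screening, heat-pattern patients fit it best. A cold-type patient has only the general and dampness items to show, 4 + 2 = 6 of 14, and could be turned away.
- If the label governs, practitioners diagnose cold-dampness by other means and the printed list does not describe what was done.

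In both cases the published definition of the population is wrong somewhere.

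**Step 5: the treatment comparison.** Sections 2.3 and 2.5 randomise eligible patients 1:1 from one pool. A wrong or mixed syndrome definition therefore acts equally on both arms before allocation. It changes whom the result applies to, without making the arms incomparable.

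**The case against.** The strongest case on the other side is that the entry rule proper, section 2.3.3, names the intended type. Section 2.3.2 refers the diagnosis to a guideline and sets no threshold, so a patient with only general or dampness signs is not clearly excluded. Section 4.4 says that the clinicians responsible for diagnosis are registered Chinese medicine practitioners, who may classify correctly whatever the article prints. The list may be a copying or translation error that never reached the clinic.

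Much of this stands, and it limits the point in four ways.

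- A reader might infer that the trial selects the opposite of its intended population. The documents do not support that: both the label and the list are written, no threshold is given, and nothing shows which is applied.
- A reader might call the whole list a heat list. It is not: 6 of its 14 items are general or dampness features.
- A reader might count the TCM syndrome score, one of the four primary outcomes in section 4.1, as affected. Its items are not described, as is common in an article, so use of the same list is only an inference. The other three primary outcomes (visual analogue scale, disease activity index and functional index) do not depend on the syndrome definition.
- The guideline is not available here, so what it lists for this type cannot be asserted.

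None of this removes the contradiction. It is not a matter of detail left to a fuller document: the article prints a complete list, and that list conflicts with the label printed above it.

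**Conclusion.** The point holds as an internal contradiction in the definition of the target population. The signs in section 2.3.2 include heat signs and no cold sign, while sections 2.3, 2.3.3 and 5 require and describe a cold type. It touches an entry criterion for all 80 patients. How many would be misclassified cannot be calculated, because the document does not say how the list is used.

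The contradiction itself rests on the printed words alone; fever and heat pain suffice. The wider tally of 8 of 14 rests on the assumed TCM reading of six items. The consequence for enrolment is conditional on the list governing screening. The harm concerns applicability and whether the stated question is answered; bias between the arms does not follow. Because the conflict is in eligibility and is cheap to remove, it should be corrected.

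**What to change.** 1. Compare the list in section 2.3.2 with the cited guideline and with the screening form in use, and establish which definition investigators apply.
2. Reconcile sections 2.3.2, 2.3.3 and 5. Either correct the list so that it describes the named type, or, if the printed list is what is applied, rename the target population throughout (title, Introduction, sections 2.1, 2.3, 2.3.2 and 2.3.3) and bring the rationale in section 5 into line.
3. State how many signs, or which combination, establish the type, so that the reconciled list can be applied uniformly.
4. Confirm that the items of the TCM syndrome score match the reconciled definition.
5. Re-check the syndrome classification of anyone already enrolled. Enrolment was planned from 1 February 2023 and the article appeared on 10 February 2023, so screening may have begun by publication; the number enrolled is not given.

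The cost is one protocol correction with ethics notification, a revised screening form (and score sheet, if its items change), and the re-check of early participants. No additional patients are needed.

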#### 2.3.3. Inclusion criteria.

The inclusion criteria are as follows: Meet the Western medical diagnostic standards of AS; TCM dialectic is cold-dampness obstruction type; 18 to 40 years old, male or female; Women of childbearing age ascertain to be non-pregnant and had no pregnancy plans for the duration of the trial; Did not take any AS treatment drugs in the 1 month period before receiving treatment; Voluntarily participate in this trial and agree to enter the clinical study, sign the informed consent form.

#### 2.3.4. Exclusion criteria.

The exclusion criteria are as follows: Patients with other rheumatic immune system diseases; Those with serious diseases such as heart, brain, lung, liver, kidney, tumor, infection or hematopoietic system; Patients who are taking other Chinese medicine treatment for certain diseases; Lactating or pregnant women; Those who are allergic to the drugs in this test; Patients with mental disorders who cannot communicate effectively; Active peptic ulcer/bleeding, sulfa allergy; Patients with severe heart failure; Patients with perioperative pain during coronary artery bypass graft.

### 2.4. Sample size

The sample size calculation was performed using PASS 15 software (https://www.ncss.com/),^[7]^ with α = 0.05 (2-tailed test). The sample size was N_1_ in the treatment group and N_2_ in the control group. According to the current clinical efficacy statistics of TCM in the treatment of AS, the effective rate of the treatment group was P_1_ = 78%, while the control group P_2_ = 43%. Using the Z test, H_0_: P_1_–P_2_ = 0. H_1_: P_1_–P_2_ = D_1_ ≠ 0, calculated using the approximate normal method, N_1_ = N_2_ = 36. Considering the loss of cases, if the loss rate is 10%, and each group increases by 4 people, the final sample size is 40 cases in the treatment group and the control group, for a total of 80 cases.

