### 2.5. Randomization and blinding

This trail will use random assignment concealment. Participants who provide informed consent and meet the inclusion criteria will be randomly assigned in a 1:1 ratio to treatment and control groups. Randomization will be based on random numbers generated by the computer. Independent researchers will prepare the distribution in an opaque envelope containing the distribution sequence number and are responsible for concealing the distribution sequence. Due to the specificity of the intervention, double-blinding was impossible. Outcome assessors, data curators will be unaware of treatment assignments.

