## 4. Outcome measures

### 4.1. Primary outcome

Visual analogue scale, bath ankylosing spondylitis disease activity index, bath ankylosing spondylitis functional index, and TCM syndrome scores will be primary indicators, which will be tested at 0th and 8th weeks of treatment.

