### 4.5. Statistical analysis

SPSS 28.0 software (https://www.ibm.com/spss) will be used by professionals blinded to trial grouping for statistical analysis of data. Efficacy and safety analyses will be based on the intent-to-treat principle of analysis of all randomized participants. Measurement data that conform to normal distribution are represented by mean and standard deviation (‾ *x ± s*), and measurement data that are not normally distributed are represented by median and quartile (M[Q _25_, Q _75_]). Qualitative data is expressed as a %. If the data obey the normal distribution and the variance is homogeneous, the *t* test would be used for comparison; if the data does not conform to the normal distribution or the variance is unequal, the nonparametric test should be used for comparison. A 2-tailed test will be used, and *P* < .05 indicated a statistically significant difference.

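### Section 2.4 sizes the trial on an undefined effective rate that is not a listed outcome, so power for the four primary scores is not shown

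*Protocol article*

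**What the plan says.** Protocol article, section 2.4, sets the error rate "with α = 0.05 (2-tailed test") and takes its planning values from clinical efficacy statistics on TCM in AS: "the effective rate of the treatment group was P_1_ = 78%, while the control group P_2_ = 43" per cent. The hypothesis is one about proportions: "Using the Z test, H_0_: P_1_–P_2_ = 0". The result is "calculated using the approximate normal method, N_1_ = N_2_ = 36". The allowance for loss is "if the loss rate is 10%, and each group increases by 4 people", giving 40 per group and 80 in total. The section states no power.

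Section 4.1 names different quantities: "Visual analogue scale, bath ankylosing spondylitis disease activity index, bath ankylosing spondylitis functional index, and TCM syndrome scores will be primary indicators", measured at weeks 0 and 8. The abstract lists the same four. Section 4.2 (ESR, CRP, spinal mobility) and section 4.3 (safety) contain no effective or response rate.

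Section 4.5 compares groups by t test, or by a nonparametric test if normality or equal variance fails. On categorical data it says only "Qualitative data is expressed as a" percentage.

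**The concern.** A sample size calculation should tell the reader what difference in the primary outcome the trial is likely to detect. Here the sizing hypothesis belongs to no listed outcome, and no listed primary outcome has a sizing hypothesis. The term effective rate occurs only in section 2.4, without a cut-off or the scale it would be derived from.

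This is more than detail left to another document. The article gives a rationale for N, but for a different endpoint. An unseen SAP could define a responder and name a test for proportions. It could not turn a two-proportion calculation into one for four scores.

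At stake is the meaning of 80 patients. A reader of section 2.4 would take the primary comparisons to be adequately powered. Nothing in the article shows whether they are, for what difference, or at what power.

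**Working it through.** **Inputs from the article.** Two-sided alpha 0.05; p1 = 0.78; p2 = 0.43; Z test by normal approximation; 36 per group; 10% loss (all section 2.4). Allocation: "randomly assigned in a 1:1 ratio to treatment and control groups" (section 2.5). Not given: the power, and any mean difference or SD for a primary score.

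**Step 1. Reproduce 36 and 40.** The unpooled two-proportion formula is n = (z_alpha/2 + z_beta)² × [p1(1 − p1) + p2(1 − p2)] / (p1 − p2)².

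- Variance term: 0.78 × 0.22 + 0.43 × 0.57 = 0.1716 + 0.2451 = 0.4167.
- Squared difference: 0.35² = 0.1225.
- At an assumed 90% power: (1.960 + 1.2816)² × 0.4167 / 0.1225 = 35.74, so 36.
- At an assumed 80% power: 26.70, so 27, which is not the stated figure.
- Loss: 36 / 0.9 = 40 per group, 80 in total.

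The stated numbers reproduce exactly with 90% power, which is an inference because the article does not state it. Power at n = 36 by the same formula is 90.2%.

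**Step 2. Look for the endpoint.** The effective rate is absent from section 4.1 (four scores), section 4.2 (laboratory and mobility measures) and section 4.3 (safety). The 90% therefore attaches to a binary endpoint that the trial does not list.

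**Step 3. What 36 per group offers for a score.** With no difference or SD in the article, the standardized difference d (difference divided by SD) has to be assumed. For a two-sample t test, power = P(T > t_crit), where T is non-central t with 2n − 2 = 70 degrees of freedom and non-centrality d × √(n/2) = d × √18.

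| Assumed d | Power, 36 per group, alpha 0.05, one outcome |
|---|---|
| 0.3 | 24% |
| 0.4 | 39% |
| 0.5 | 55% |
| 0.6 | 71% |
| 0.7 | 83% |
| 0.8 | 92% |
| 0.85 | about 95% |

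If all 40 per group are evaluable, power at d = 0.5 is 60%.

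**Step 4. Solve for the detectable difference, 36 per group.**

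| Two-sided alpha | d for 80% power | d for 90% power |
|---|---|---|
| 0.05 (one score) | 0.670, state as 0.67 | 0.775, state as 0.78 |
| 0.05 / 4 = 0.0125 (split over four) | 0.805, state as 0.81 | 0.911, state as 0.92 |

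The 90% values are rounded up so that the stated power is reached; d = 0.77 would give just under 90%.

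**Step 5. What 78% v 43% would mean on a score.** This assumes that response is a cut on a latent score of logistic or normal shape, which the article does not say.

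- Logistic: [ln(0.78/0.22) − ln(0.43/0.57)] × √3/π = (1.266 + 0.282) × 0.551 = 0.853 SD.
- Normal: 0.772 − (−0.176) = 0.949 SD.

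At 0.853 to 0.949 SD, 36 per group give 95% to 98% power at alpha 0.05, and 85% to 92% at alpha 0.0125.

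**The case against.** The strongest defence is that N may well be adequate. If the sponsor's expected advantage carried over to a score as in step 5, power would be at least 85% even with alpha split four ways. That stands, and it is why a reader who infers that the trial is underpowered goes too far: the values 0.4 and 0.5 SD are illustrations and appear nowhere in the article. The favourable values rest equally on an unstated conversion, so they do not supply the missing justification.

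Three other strong readings are not supported.

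- **That 36 is miscalculated.** The pooled-variance form would ask for 39 per group at 90% power. Section 2.4 does not specify pooling, and the unpooled normal approximation is a legitimate Z test. This is a choice of method.
- **That the effective rate has no analysis.** A responder definition and a test for percentages are commonly left to the full protocol or SAP, and the unspecified nonparametric test in section 4.5 does not exclude a comparison of proportions. Their absence from an article is no fault in itself.
- **That a null result on BASDAI or VAS could not be interpreted.** The estimate and its confidence interval would remain, whatever endpoint was used for planning. What is lost is the ability to set that result against a planned difference.

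The mismatch survives all of this. A responder rate might be derivable from the TCM syndrome score, but section 4.1 names the score itself as the outcome.

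**Conclusion.** The point holds as an endpoint mismatch. The stated size is tied to a binary quantity that is neither defined nor listed as an outcome, and its target power is unstated. The arithmetic is correct given an assumed 90% power and the unpooled formula.

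Power for each of the four primary scores is not shown. Depending on a standardized difference that the article does not give, 36 evaluable per group could mean 39% power (0.4 SD), 55% (0.5 SD) or about 95% (0.85 SD). These figures assume a two-sample t test on one outcome, two-sided alpha 0.05, and the 10% loss allowed for in section 2.4. Whether the trial is underpowered cannot be decided from the document.

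**What to change.** Keep N = 80. Keep the effective-rate calculation in section 2.4 as the original basis of N, with its power stated. Then take one of two routes.

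1. **Restate for a score.** Add a dated statement to section 2.4 along these lines: *36 evaluable patients per group give 80% (90%) power to detect a standardized difference of 0.67 (0.78) in [one named primary score] at week 8, two-sided alpha 0.05.* If alpha is split over the four primaries (0.0125 each), the differences become 0.81 (0.92). Translate them to scale points with a cited SD, and say whether a difference of that size is plausible and important, since the statement is solved backwards from a fixed N. The sponsor should choose the score.
2. **Adopt the effective rate.** Define it, name it as the single primary outcome, and state its power (90% if the unpooled Z calculation was intended) and its test. This also changes sections 4.1 and 4.5 and the abstract.

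The date matters because the trial status section puts the start of enrolment at February 1, 2023, before publication on February 10, 2023.

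**Cost.** No more patients and no change to treatment. Route 1 adds a few sentences to one paragraph; route 2 changes the primary outcome and needs more text. Under route 1 the stated justification becomes less favourable, because it will show that only fairly large differences can be detected with high power.
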